**Fig. 1 Fig1:**
[figure not shown]
CONSORT study flow diagram of this study protocol

The end of this trial is the date of the 12-month follow-up visit of the last participant. At the end of the trial, participants will resume standard practice of care according to the hospital’s routine follow-up schedule after discectomy.

### Blinding

This is a single (assessor) blind trial comparing biportal endoscopic discectomy with standard treatment (microscopic discectomy); the participants and surgeons will know what surgery they have undergone. Therefore, only the assessor will be blinded, and the blinded outcome assessor will measure and collect all outcomes before and after surgery, with a single-blind in each hospital. Each assessor will attend a training session prior to data collection to ensure consistency across hospitals. The outcome assessor will provide a detailed justification if unblinding occurs.

### Interventions

#### Active intervention: biportal endoscopy

The biportal endoscopic discectomy has been previously described in several studies [9, 14, 15]. This surgical technique is similar to microscopic discectomy except that it involves making two portals. Therefore, the most important point of this surgical technique is creating a viewing portal for the camera and a working portal for the spinal instrument, which provides working space. The portal position starts from 0.5 to 1 cm lateral to the spinous process. With a right-handed surgeon and left-side approach as a reference, the working portal makes an incision about 1 cm below the lamina. The viewing portal is made vertically 1 cm proximal to the working portal with a 7-mm incision. When approached from the right side, the viewing portal is made vertically 1 cm distally to the working portal with a 7-mm incision. After creating the two portals, the paraspinal muscles will be detached from the lamina using a narrow Cobb elevator to ensure adequate working space. A 4-mm, 30° arthroscope is inserted through the viewing portal under saline irrigation with a pressure of 30-40 mm Hg. Surgery is performed by inserting the spinal surgical instruments, such as bipolar radiofrequency cauterization, burrs, Kerrison punches, and pituitary rongeurs, through the working portal. The frazzle muscle and soft tissue are removed using a shaver and bipolar radiofrequency cauterization. After the working space is created, the discectomy is performed in the same way as the microscopic discectomy (Fig. 2).

**Fig. 2 Fig2:**
[figure not shown]
**A** Operative field of biportal endoscopic spine surgery in right-handed surgeon. **B** Intraoperative endoscopic view showed extruded disc(*)compressing nerve root

#### Control intervention: microscopic surgery

The microscopic discectomy procedure is a commonly used surgical technique for patients with a herniated disc. Briefly, the surgery level is checked by fluoroscopy, and a 3-cm midline incision is made. Following the skin incision, the paraspinal muscle is detached from the spinous process and the lamina using a Cobb elevator and towed with a Taylor retractor. Laminotomy is performed using burr and Kerrison punches. After removing a partial ligamentum flavum under the lamina, the dura and root are checked for discectomy. The root is retracted, and the disc is removed below the root, following which a check for any remnant disc is performed, and the operation is completed.

### Outcome measures

#### Primary outcome

The primary outcome will be the biportal endoscopic discectomy efficacy in the lumbar herniated disc. The efficacy will be determined by the Oswestry Disability Index (ODI) score [17]. The primary outcome is the ODI score 12 months after surgery between the two groups. The ODI is the most commonly used outcome measure questionnaire for lumbar disabilities in a hospital setting. This questionnaire is designed to evaluate various daily life activities, divided into ten sections. Each section is scored on a scale of 0-5, with a score of 5 representing the greatest disability. The ODI score is the summed score divided by the total possible score and expressed as a percentage (i.e., multiplied by 100). For all unanswered questions, the total possible score is reduced by 5. If the patient marks more than one statement in a question, the statement with the highest score is recorded as an indication of the actual disability.

#### Secondary outcome

The secondary outcomes are the clinical outcomes, radiographic outcomes, and adverse events. Clinical outcomes include (1) low back pain and lower extremities radiating pain, measured based on the VAS pain score, which ranges from zero (i.e., “none”) to 10 (i.e., “severe pain”), (2) quality of life (QOL), measured by the EuroQol-5-dimension-5-level [EQ-5D] questionnaire, which contains five questions with five responses for each question, and the total score is converted into the final EQ-5D value, ranging from 0.000 to 1.000; higher scores indicate a better QOL [18], (3) surgery satisfaction, (4) walking time, (5) the postoperative return to daily life period, (6) postoperative surgical scarring, measured by the Patient and Observer Scar Assessment Scale [POSAS] patient scale 2.0, containing six parameters with 10-point scoring system; 6 represents normal skin, and 60 represents the worst scar imaginable, and (7) surgery-related variables, such as postoperative drainage (mL), operation time (minutes), admission duration (hours), postoperative creatine kinase, and implementation status of conversion to open surgery. The radiographic outcomes include (1) the degree of disc removal and facet joint injury, measured using postoperative MRI or CT and (2) other radiographic complications, measured using simple radiographs during the follow-up period. Safety will be assessed by evaluating all adverse and severe adverse events and surgery-related effects (reported to the appropriate institution, as needed). This will be reported by the participant to the surgeon or the assessor and recorded in the electronic database.

Baseline radiographs will be made in the anteroposterior, lateral, flexion, and extension view, and spondylolisthesis and segmental instability at the surgery level will be scored. A preoperative spine MRI will be systematically checked. Based on the lumbar disc nomenclature of David F. Fardon et al., extruded, sequestrated, and migrated disc will be classified according to disc type, and central canal zone, subarticular zone will be classified according to location [19]. The degree of annular defect of the disc will be evaluated through Carragee classification [20]. Also, disc herniation side and severity of the canal compromise in the axial plane will be checked. Patient-reported outcomes will be collected from the participants at baseline and at 2 weeks and 3, 6, and 12 months after surgery. These outcomes will be collected by the blinded assessor and recorded in the eCRF system (Table 1).

**Table 1 Tab1:** Evaluation schedule

Visit type	Screening	Operation/treatment	Follow-up			
Visit	1	2	3	4	5	6
Visit week	− 4~0 weeks	0–2 day	2 weeks	12 weeks	24 weeks	52 weeks
			± 5 days	± 4 weeks	± 8 weeks	± 8 weeks
Informed consent	■					
Demographics*	■					
Inclusion/exclusion	■					
Randomization		■				
Operation		■				
MRI (or CT)†	■	■				
Simple radiographs	■		■	■	■	■
ODI	■		■	■	■	■
EQ-5D-5L	■		■	■	■	■
VAS	■		■	■	■	■
POSAS				■	■	■
Other surveys^‡^			■	■	■	■
Adverse events		■	■	■	■	■

*MRI* magnetic resonance imaging, *CT* computed tomography, *ODI* Oswestry Disability Index, *EQ-5D-5L* EuroQol 5 Dimension 5 level, *VAS* visual analog scale, *POSAS* Patient and Observer Scar Assessment Scale

*Baseline patients’ characteristics including past medical/surgical history, physical examination, and laboratory tests

^†^CT scan is possible when MRI cannot be taken

^‡^Including surgery satisfaction, walking time, postoperative return to daily life period

#### Statistical analysis

All statistical analyses will be conducted using Stata/MP 15.1 (StataCorp LLC, College Station, TX). A two-sided *P*-value < 0.05 will be considered statistically significant. The Shapiro-Wilk test will be used to evaluate the distribution of the collected data. Normally distributed continuous variables will be presented as the mean and standard deviation (SD), whereas non-normally distributed variables will be presented as the median and interquartile range. Categorical variables will be presented as numbers and percentages (%).

Both modified intention-to-treat (mITT) and per-protocol analyses will be performed. The mITT strategy will be the main analysis and indicates that participants are analyzed on whether they underwent a randomly assigned surgery (to avoid the effects of crossover and dropout, which may break the random assignment to the treatment groups). Excluded participants before and after surgery will be excluded from the analysis, and participants exceeding the calculated sample size will not be recruited.

The surgical intervention effect 12 months after surgery will be assessed by the ODI scores and a two-sided 95% confidence interval (CI) as the primary outcome and then compared between the groups. Biportal endoscopic discectomy will be considered equivalent to microscopic discectomy if the upper and lower limit of 95% CI of the ODI score at 12 months is limited to within the pre-defined equivalence limit of 12.8 points. To analyze the serial effect on secondary clinical outcomes (i.e., VAS pain scores for the back and lower extremities and the ODI, EQ-5D, and POSAS score), a linear repeated-measures mixed model will be used. Time will be analyzed as a categorical variable (2 weeks and 3, 6, and 12 months) and include the intervention-time interaction to analyze the effects of surgery during the follow-up periods. Inter-group differences during the 12-months will also be analyzed using a linear repeated-measures mixed model, controlling for baseline and follow-up time points as categorical variables. Other clinical, radiographic outcomes and adverse effects between two groups will be analyzed using Student’s *t*-test for continuous variables and the chi-square test for categorical variables.

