**Methods:**

This prospective multicenter randomized controlled equivalence trial is designed to compare the efficacy and safety outcomes of patients who underwent lumbar discectomy using biportal endoscopy or microscopy. We will include 100 participants (50 per group) with a lumbar herniated disc. The primary outcome will be the Oswestry Disability Index (ODI) score 12 months after surgery based on a modified intention-to-treat strategy. The secondary outcomes will include the visual analog scale score for low back and lower extremity radiating pain, the ODI score, the Euro-Qol-5-Dimensions score, surgery satisfaction, walking time, postoperative return to daily life period, postoperative surgical scar, and surgery-related variables, such as postoperative drainage, operation time, admission duration, postoperative creatine kinase, and implementation status of conversion to open surgery. Radiographic outcomes will also be analyzed using magnetic resonance imaging (MRI) or computed tomography (CT) and simple radiographs. Safety will be assessed by evaluating all adverse and severe adverse events and surgery-related effects. The participants will be assessed by a blinded assessor before surgery (baseline) and 2 weeks and 3, 6, and 12 months after surgery.

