### Randomization and follow-ups

Participants will be randomized into either the control (microscopy) or intervention (biportal) group at a 1:1 ratio, following a computer-generated randomization list prepared by a researcher with block sizes of four. The randomization lists will be incorporated into a web-based eCRF platform (iCReaT; internet-based clinical research and trial, icreat.nih.go.kr) accessible to authorized researchers. The randomization process will be processed independently at each hospital and completed by the researchers. Allocation will be concealed in opaque envelopes numbered consecutively and presented to the surgeon immediately before surgery.

Participants will visit the hospital for a minimum of 12 months at 2 weeks, 3 months, 6 months, and 12 months after surgery to evaluate the participant’s outcome. The participant’s primary and secondary outcomes will be collected by an independent researcher during in-hospital visits but can be evaluated over the phone if unavoidable circumstances arise (Fig. 1).

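### The main modified ITT set, read plainly, is close to a per-protocol set, its stated rationale is inverted, and no as-randomised analysis stands beside it

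*Protocol article*

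**What the plan says.** The abstract of the protocol article names the analysis behind the primary outcome: "The primary outcome will be the Oswestry Disability Index (ODI) score 12 months after surgery based on a modified intention-to-treat strategy". The Statistical analysis section defines that strategy: "The mITT strategy will be the main analysis and indicates that participants are analyzed on whether they underwent a randomly assigned surgery". It gives the purpose as "to avoid the effects of crossover and dropout, which may break the random assignment to the treatment groups", and then adds "Excluded participants before and after surgery will be excluded from the analysis". No reasons for exclusion are listed.

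The same section announces a second analysis: "Both modified intention-to-treat (mITT) and per-protocol analyses will be performed". It does not say how the two populations differ.

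Three other places bear on the point:
- Randomization and follow-ups: "Allocation will be concealed in opaque envelopes numbered consecutively and presented to the surgeon immediately before surgery".
- Blinding: only the outcome assessor is blinded; surgeons and participants know the operation.
- Secondary outcome: the surgery-related variables include "implementation status of conversion to open surgery". The article does not say whether a converted participant stays in the main set.

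**The concern.** Randomisation makes the arms comparable at the moment of allocation. Crossover and dropout do not undo that as long as everyone is counted in the arm to which they were allocated. Selecting on what happened afterwards does undo it. The article gives protection of the random assignment as its reason for a step that weakens it.

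The setting makes this more than a matter of wording. Surgeon and patient both know the operation, so a decision to switch, withdraw or exclude after surgery can depend on the arm and on the early course. The exclusion sentence sets no limit on the reasons.

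The per-protocol analysis is the natural safeguard, but it protects only if it differs from the main analysis in a known way. If the main set already requires the assigned operation and already drops later exclusions, the two sets may largely coincide. At stake is the trial's one confirmatory claim, which would not clearly describe the effect of being allocated to biportal surgery.

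**Working it through.** **Inputs from the article.** Equivalence limit 12.8, SD 17.1, power 0.90, follow-up loss 20% and 50 per group (Sample size); two-sided 95% CI inside ±12.8 (Statistical analysis).

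**Inputs assumed.** The number of participants removed, how much worse their ODI is, and the crossover rates. The article gives none of these.

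**1. The plan's own figure.** 50 × (1 − 0.20) = 40 evaluable per group. Two one-sided t-tests at 0.05 each, with a true difference of 0, need 40 per group (power 0.906), and 40 / 0.80 = 50. The stated size therefore reproduces. Under the stated 95% CI rule (0.025 per side), 40 per group gives power of 82.2%. That gap is a separate matter; it is noted here only because 82.2% is the baseline in step 4.

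**2. Standard error and decision rule.** SE = 17.1 × √(2/40) = 3.82. With 78 degrees of freedom the critical t is 1.99. Equivalence is declared when the estimate ± 1.99 × (estimated SE) lies inside ±12.8. The probabilities below integrate over the sampling distribution of the estimated variance.

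**3. Size of a shift.** If a fraction f of one arm is removed and those participants average E points worse than the rest of that arm, the arm mean falls by f × E:
- 3 of 40, E = 20: 0.075 × 20 = 1.5 points
- 4 of 40, E = 20: 0.10 × 20 = 2 points
- 4 of 40, E = 30: 0.10 × 30 = 3 points

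**4. Chance of declaring equivalence when the loss falls on the biportal arm only** (difference = biportal minus microscopic; higher ODI is worse):

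| Shift in biportal mean | True difference +12.8 (biportal worse) | True difference 0 | True difference −12.8 (biportal better) |
|---|---|---|---|
| 0 | 2.5% | 82.2% | 2.5% |
| 1.5 | 5.8% | 79.0% | 0.9% |
| 2 | 7.4% | 76.5% | 0.7% |
| 3 | 11.8% | 69.9% | 0.3% |

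The table holds 40 per arm throughout. With 37 v 40 analysed, the 1.5-point case at +12.8 gives 5.7% instead of 5.8%. Only the +12.8 column moves towards a false claim; in the other two the same loss works against declaring equivalence.

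**5. The opposite hazard, in a fully as-randomised analysis.** Let c be the crossover proportions of the two arms added together, with crossovers taking the mean outcome of the operation they received. A true 12.8 shrinks to 12.8 × (1 − c):
- c = 5%: 12.16, false equivalence 3.6%
- c = 10%: 11.52, false equivalence 5.2%
- c = 20%: 10.24, false equivalence 9.7%

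This is of the same order as step 4, so neither analysis is safe alone.

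**The case against.** The best defence has five parts.

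**The wording is unclear and per-protocol is named separately.** A reader might infer that the main analysis simply is per-protocol. The article does not say so, and the per-protocol set is undefined, so near-identity cannot be shown. This stands, and it limits the point to the plain reading. It does not remove the point: the purpose of avoiding crossover and dropout, and the exclusion after surgery, are stated rules and not details left to a fuller document.

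**Conversions.** A reader might infer that biportal cases converted to open surgery are dropped and that the loss falls on one arm. No section says converted cases leave the analysis, and no conversion rate is given for either arm. Conversion is itself a secondary outcome, which sits better with keeping those cases. This stands; conversion is only an event whose handling is unstated.

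**Direction.** A reader might infer that the rule biases towards equivalence. The sign depends on which arm loses which outcomes and on the true difference, as the table shows. This stands.

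**Little room before surgery.** The evaluation schedule (Table 1) puts randomisation at the operation visit, and the surgeon learns the allocation just beforehand. That limits losses before the operation, but exclusions after surgery remain open for 12 months.

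**Intention-to-treat has its own problem in an equivalence trial.** Crossover dilutes a true difference. This also stands, and it is a reason to require both analyses, not to leave out the as-randomised one.

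**Conclusion.** The concern holds in limited form. The main analysis of the primary outcome is tied to receipt of the assigned operation and to not being excluded later. The justification is the wrong way round, and the article states no as-randomised analysis against which to read the result.

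The size is illustrative. With 40 per arm, SD 17.1 and the 95% CI rule, an assumed loss of poor biportal outcomes worth 1.5 to 3 points raises false equivalence at a true difference of 12.8 from 2.5% to between 5.8% and 11.8%. With no true difference, the same loss lowers the chance of success from 82.2% to between 79.0% and 69.9%. The counts and ODI gaps behind those shifts are assumptions. The figures show that a few selective exclusions can matter; they do not predict what will happen. The documents support neither a fixed bias towards equivalence nor a selective loss of converted biportal cases.

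**What to change.** 1. Define the main set as all randomised participants in whom surgery was started, analysed in the arm to which they were randomised, including crossovers and any conversions or re-operations.
2. Delete the sentence that removes participants excluded after surgery, and delete the rationale about crossover and dropout.
3. Define the per-protocol set separately, as those who received the assigned surgery.
4. Claim equivalence only if the 95% CI lies within ±12.8 in both analyses.

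**Cost.** The change needs amended wording and continued follow-up to 12 months of participants who would otherwise have been removed. Two statistical costs should be stated openly. Crossovers kept as randomised pull a true difference towards zero (false equivalence of about 3.6% to 9.7% at the margin for an assumed 5% to 20% crossover), which is why the per-protocol result must agree. Requiring both analyses to succeed also slightly lowers the chance of declaring equivalence.

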#### Sample size

This trial will recruit 100 participants (50 participants per group) to confirm the primary outcome equivalence between biportal endoscopic and microscopic discectomy. According to a previous report [21], the minimal clinically important ODI difference was 12.8, and in the previous study [22], the standard deviation of the ODI value 1 year after endoscopic discectomy was 17.1. Assuming that the equivalence limit is 12.8, alpha = 0.05, power = 0.90, two-sided 95% CI, and the follow-up loss = 20%, 50 participants are needed for each group. Power Analysis and Sample Size software version 15 (NCSS, Kaysville, UT, USA) was used for calculating the sample size.

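### The per-visit mixed model for VAS, ODI and EQ-5D is stated without a baseline term, and the next sentence leaves the role of baseline open

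*Protocol article*

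**What the plan says.** The protocol article's Statistical analysis section gives two consecutive mixed-model statements for the secondary clinical outcomes, listed as "VAS pain scores for the back and lower extremities and the ODI, EQ-5D, and POSAS score".

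- **Serial-effect model.** "Time will be analyzed as a categorical variable (2 weeks and 3, 6, and 12 months) and include the intervention-time interaction". No baseline term is named.
- **Overall comparison.** "Inter-group differences during the 12-months will also be analyzed using a linear repeated-measures mixed model", and this is done "controlling for baseline and follow-up time points as categorical variables". No interaction is named.

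On data collection, the Secondary outcome section says: "Patient-reported outcomes will be collected from the participants at baseline and at 2 weeks and 3, 6, and 12 months after surgery". Table 1 confirms this for ODI, EQ-5D-5L and VAS. POSAS differs: Table 1 schedules it only at 12, 24 and 52 weeks, with no baseline and no 2-week value.

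The primary analysis is described separately. It sets the two-sided 95% confidence interval for 12-month ODI against the limit of 12.8, and it is not said to come from either mixed model.

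**The concern.** Two things need attention.

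First, a baseline score is collected for four of the five listed outcomes, but the model that yields the visit-by-visit differences does not use it. Under randomisation this causes no bias. It gives up precision that is already paid for, in a trial planned on 50 patients per group.

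Second, baseline does appear in the next sentence, but in wording that has two meanings. If the categorical qualifier governs only the follow-up time points, baseline is a covariate and the sentence agrees with the previous one. If it governs baseline as well, the pre-operative visit becomes a fifth level of the outcome's time factor. A single group coefficient with no interaction would then average over an occasion before surgery, where randomisation makes the expected difference zero. At stake is the size of the overall 12-month difference in back pain, leg pain, disability and quality of life. An analyst could fit either model and claim to have followed the text.

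**Working it through.** **Inputs.** From the protocol article: ODI SD at one year 17.1; 50 per group; 20% loss to follow-up, so 50 × 0.80 = 40 evaluable per group; four follow-up visits plus baseline. The article gives no within-patient correlations and no covariance structure, so those used below are assumptions. It also gives no figure for the mixed models that could be reproduced. Its sample size concerns the primary comparison: two one-sided t tests at 0.05 per side give 40 evaluable, and 40/0.80 = 50. Whether that level suits a 95% interval is a separate matter.

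**1. Precision lost in the per-visit model.** With correlation r between baseline and a visit, adjusting for baseline multiplies the standard error of that visit's difference by √(1 − r²). Omitting it therefore inflates the standard error by 1/√(1 − r²).

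For ODI, unadjusted: 17.1 × √(2/40) = 3.82 points.

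| Assumed r | Adjusted SE | Inflation if omitted |
|---|---|---|
| 0.3 | 3.82 × 0.954 = 3.65 | 1.05 |
| 0.4 | 3.82 × 0.917 = 3.50 | 1.09 |
| 0.5 | 3.82 × 0.866 = 3.31 | 1.15 |

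The ratios apply equally to VAS and EQ-5D; the point values are for ODI only.

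**2. The two meanings of the overall comparison.** Without an interaction, the group coefficient is a weighted mean of the visit-specific differences, with weights V⁻¹1/(1′V⁻¹1). If the true difference is zero at baseline and constant afterwards, the weight on baseline is the proportion lost.

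Mixed models fitted to simulated data, with a difference of exactly 5.0 at every follow-up visit and 0 at baseline, gave:

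- baseline score as covariate, four follow-up levels: 5.0, nothing lost;
- five time levels, no interaction, random intercept: 4.0, a loss of 1/5;
- five time levels with the group-by-time interaction: 12-month difference 5.0, nothing lost.

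**3. How far the 1/5 depends on the covariance.** With an exchangeable structure the baseline weight is 1/5 whatever the correlation. Otherwise let c be the covariance of baseline with each follow-up, s² the baseline variance relative to a follow-up variance of 1, and v = (1 + 3ρ)/4 the variance of the follow-up mean, where ρ is the correlation between follow-ups. Then the baseline weight is (v − c)/(s² + v − 2c).

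- ρ = 0.6, c = 0.5, s = 1: v = 0.70; 0.20/0.70 = 0.29.
- ρ = 0.7, c = 0.3, s = 1: v = 0.775; 0.475/1.175 = 0.40.
- ρ = 0.7, baseline correlation 0.3, s = 1.2 (c = 0.36): 0.415/1.495 = 0.28.
- ρ = 0.7, baseline correlation 0.3, s = 0.8 (c = 0.24): 0.535/0.935 = 0.57.
- First-order autoregressive with correlation 0.7: 0.34.

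So under the five-level meaning without interaction, the loss was 20% with exchangeable covariance and 28% to 57% in the other cases tried. Under the covariate meaning it is zero.

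**4. Outcomes the second meaning could reach.** POSAS has no baseline value, so nothing can be diluted. The per-visit contrasts come from the interaction model, which has follow-up levels only. Outcomes analysed by t-test or chi-square are not in these models. The primary ODI comparison is not stated to use them.

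**The case against.** The strongest reply is that the two sentences describe two analyses with different targets and do not conflict. The first sentence already fixes time as the four follow-up visits. The second then repeats that coding and adds an adjustment for baseline. The verb used for the adjustment is ordinary covariate language, and Table 1 places baseline at screening, outside the 12 months that the comparison covers. Omitting baseline from the serial model is also no error, since the estimate stays unbiased. Coding details and the covariance structure are commonly left to an analysis plan.

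Most of this stands. The covariate meaning is at least as natural as the other. The missing baseline term is a matter of efficiency, and the undeclared covariance structure is no finding. Two things remain. Even on the favourable meaning, the per-visit model lacks an adjustment that the overall comparison has. And because the baseline scores are numeric, the categorical qualifier gives the five-level meaning some textual support, so the wording does not exclude it.

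A reader might go further and infer that the plan defines its time factor in two contradictory ways, so that every between-group difference shrinks by about 20% in favour of the hypothesis of similarity. The document does not support that. The shrinkage needs one particular meaning, no interaction, an exchangeable covariance and a constant effect. It would touch one overall coefficient for four secondary outcomes. The equivalence decision is not shown to depend on it, and faster early recovery would still appear in the 2-week and 3-month contrasts of the serial model.

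**Conclusion.** The point holds as an improvement to the secondary analyses. It is not an established bias.

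- **Per-visit model.** As stated it ignores the baseline score for back and leg VAS, ODI and EQ-5D. Its standard errors are about 5% to 15% larger than they need be if the baseline correlation lies between 0.3 and 0.5, a range that is assumed here.
- **Overall comparison.** The sentence admits two models. One has no bias. The other gives 4/5 of a constant true difference under a random intercept without interaction, and less in the other covariance structures tried. The document does not settle which is meant.
- **Not shown to be affected.** The primary 12-month ODI comparison, the per-visit contrasts, POSAS, and the outcomes tested by t-test or chi-square.
- **POSAS.** Neither the four-level time factor nor a baseline adjustment fits its schedule in Table 1.

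**What to change.** Replace the two sentences with one model per outcome:

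- **Response:** follow-up values only, at 2 weeks and 3, 6 and 12 months.
- **Fixed effects:** group, follow-up time as a categorical factor, group-by-time, and the patient's own baseline score of that outcome as a continuous covariate where it is collected.
- **POSAS:** the same model without a baseline term and with the three visits in Table 1.
- **Estimates:** the difference at each visit and the average difference over the 12 months, both as contrasts from this one model.

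This adds the missing adjustment to the per-visit estimates, rules out the diluting meaning, and makes the per-visit and average results consistent with each other. The cost is one or two sentences of analysis wording, best settled before outcome data are compared by group. It needs no new data, no extra visits and no more patients.

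### Return to daily life is a duration with no scheduled observation after the 12-month visit, yet the residual rule sends it to Student's t-test, which cannot handle patients who have not returned

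*Protocol article*

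**What the plan says.** The Secondary outcome section lists, among the clinical outcomes, item "5) the postoperative return to daily life period". Unlike drainage, operation time and admission duration in the same list, it has no unit. Table 1 collects it under other surveys, whose footnote reads "Including surgery satisfaction, walking time, postoperative return to daily life period". These surveys are ticked at 2, 12, 24 and 52 weeks, the last with a window of ± 8 weeks. No later visit is planned: "The end of this trial is the date of the 12-month follow-up visit of the last participant".

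The Statistical analysis section assigns a repeated-measures mixed model to a closed list: "VAS pain scores for the back and lower extremities and the ODI, EQ-5D, and POSAS score". Return to daily life is not on it. For what remains, the rule is "Other clinical, radiographic outcomes and adverse effects between two groups will be analyzed using Student’s *t*-test for continuous variables", and otherwise the chi-square test. No survival or rank method is named. The Shapiro-Wilk test decides only how data are summarised, not which test is used.

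**The concern.** A period from surgery until a patient resumes daily life is a time to event. Its observation ends at the 12-month visit, or earlier for patients lost to follow-up. A patient who has not returned by then has a censored time: it is known only to exceed the time of last contact.

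A t-test has no place for such a value. The analyst must either omit the patient, which restricts the comparison to those who recovered, or enter the last visit as though return happened that day. At stake is whether this secondary outcome describes recovery in everyone operated on or only in those who did well. The Discussion cites earlier functional recovery with the biportal technique in previous work, so readers are likely to look at this result.

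**Working it through.** **Which test applies.** The mixed-model list is closed and omits this outcome. The next sentence covers all other clinical outcomes. A duration is continuous, so it falls to the t-test. This is reached through the residual category; the outcome is not named there.

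**Inputs from the document.** Surveys at 2, 12, 24 and 52 weeks; final window ± 8 weeks, so the last visit falls between 52 − 8 = 44 and 52 + 8 = 60 weeks; 50 patients per arm. The plan gives no design figure for this outcome, so there is none to reproduce.

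**Assumed inputs (not in the document).** Share not returned, p, and mean time among returners, m = 6 weeks in both arms, with every returner back before the horizon H.

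**Option 1, omit non-returners.** The restricted mean time not yet returned is (1 − p)·m + p·H. With H = 52:

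- 5% not returned: 0.95 × 6 + 0.05 × 52 = 5.7 + 2.6 = 8.3 weeks
- 15% not returned: 0.85 × 6 + 0.15 × 52 = 5.1 + 7.8 = 12.9 weeks
- difference: 4.6 weeks, against an expected difference of 6 − 6 = 0 among returners

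With equal m the missed amount is (p1 − p0)(H − m):

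| Not returned | Missed, H = 52 |
|---|---|
| 0% vs 0%, or 5% vs 5% | 0 |
| 5% vs 10% | 0.05 × 46 = 2.3 weeks |
| 5% vs 15% | 0.10 × 46 = 4.6 weeks |
| 5% vs 20% | 0.15 × 46 = 6.9 weeks |

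At H = 44, the earliest in-window final visit, the 5% versus 15% case gives 0.10 × (44 − 6) = 3.8 weeks.

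**Direction.** In general the full difference is (m1 − m0) + p1(H − m1) − p0(H − m0), and a returners-only comparison sees only m1 − m0. The rest can have either sign, so omission can hide, create or reverse a difference.

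**Option 2, enter the last visit.** A patient lost after the 2-week visit without having returned is scored as 2 weeks, faster than the assumed 6-week average of returners. One who reaches the final visit without returning is scored anywhere from 44 to 60 weeks, depending on the appointment. The first error makes an arm with more early loss look quicker. The second adds noise of up to 60 − 44 = 16 weeks.

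**Effect on the tests.** Simulation with 40 evaluable per arm (50 × 0.80), 4000 runs, lognormal return times with median 6 weeks and log-SD 0.8 in both arms, cut-off at 52 weeks:

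| Not returned | t-test, returners only | Log-rank, censored |
|---|---|---|
| 0% vs 0% | 4.5% | 4.6% |
| 5% vs 5% | 4.9% | 4.8% |
| 5% vs 15% | 4.8% | 21% |
| 5% vs 25% | 4.3% | 59% |
| 10% vs 30% | 5.7% | 52% |

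Entries are the share of runs with p < 0.05. The flat t-test column is built in, since returners have the same distribution in both arms. The table shows that the t-test cannot see a difference in non-return; it does not show that such a difference will occur.

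**The case against.** The strongest reply is that the article never says how this item is recorded. It sits in a survey repeated at four visits and has no unit. If it is a returned/not-returned status at each visit, chi-square applies, non-returners stay in, and the problem disappears. That reading is possible but strained, because a period is a duration. It is why the point is conditional on the item being recorded as one.

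A second reply is that coding rules for unreturned patients belong in the analysis plan. That stands for the coding rule: a reader might infer that the protocol says non-returners are dropped, and it does not. It does not rescue the choice of test, which the article states and a faithful analysis plan would inherit.

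Third, the 20% follow-up loss might be read as the share missing from this comparison. It is an allowance in the ODI sample size. A patient who returned early and was lost later can already have a recorded duration; only loss before return matters, and no figure is given for that.

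Finally, the sizes rest on assumed non-return rates. A year after a one-level discectomy the true share may be very small, and then the two tests agree. This stands.

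**Conclusion.** The point holds for one secondary outcome, provided it is recorded as a duration. The stated method does not suit a time that is censored for some patients, and neither way of forcing those patients into a t-test is sound. The size ranges from nothing, when almost everyone returns, to about 4.6 weeks of restricted mean time missed under the assumed 5% versus 15% not returned, 6-week mean among returners and 52-week horizon.

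Two stronger conclusions are not supported. A reader might infer a bias toward finding the operations similar, but the direction depends on who fails to return and who is lost, and is not fixed. A reader might also infer a threat to the equivalence claim. That claim rests only on the 12-month ODI against 12.8 points, which this outcome does not enter.

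**What to change.** Take return to daily life out of the t-test sentence and give it its own: time from surgery to return, with patients who have not returned censored at last contact. Compare arms by Kaplan-Meier with a log-rank test, or by the difference in restricted mean time with its 95% CI. The horizon should be common to both arms and supported by all visit windows; 44 weeks is the earliest in-window final visit. If only status per visit is recorded, use interval-censored methods. Report the proportion not returned by the 12-month visit in each arm.

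The cost is slightly more analysis work and a summary less familiar to readers than a mean. No extra patients or visits are needed.
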